# Hypofractionated helical intensity-modulated radiotherapy of the prostate bed after prostatectomy with or without the pelvic lymph nodes - the PRIAMOS trial

**DOI:** 10.1186/1471-2407-12-504

**Published:** 2012-10-31

**Keywords:** Prostate cancer, Radiotherapy, Hypofractionation, Helical tomotherapy, Prostate bed, Pelvic lymph nodes

## Abstract

**Background:**

While evidence on safety and efficacy of primary hypofractionated radiotherapy in prostate cancer is accumulating, data on postoperative hypofractionated treatment of the prostate bed and of the pelvic lymph nodes is still scarce. This phase II trial was initiated to investigate safety and feasibility of hypofractionated treatment of the prostate bed alone or with the pelvic lymph nodes.

**Methods/design:**

A total of 80 prostate cancer patients with the indication for adjuvant radiotherapy will be enrolled, where 40 patients with a low risk of lymph node involvement (arm 1) and another 40 patients with a high risk of lymph node involvement (arm 2) will each receive 54 Gy in 18 fractions to the prostate bed. Arm 2 will be given 45 Gy to the pelvic lymph nodes additionally. Helical Tomotherapy and daily image guidance will be used.

**Discussion:**

This trial was initiated to substantiate data on hypofractionated treatment of the prostate bed and generate first data on adjuvant hypofractionated radiotherapy of the pelvic lymph nodes.

**Trial registration:**

ClinicalTrials.gov; NCT01620710

## Background

With 58.000 newly diagnosed cases every year in Germany, prostate cancer is the most common cancer of men in Germany. As the proportion of men older than 60 years is estimated to rise with the demographic shift up to 37% in 2050, prostate cancer will gain more and more epidemiological and economical significance [1]. For patients with localised prostate cancer, radical prostatectomy and definitive radiotherapy are primary treatment options. The guidelines of the German Society of Urology strongly recommend postoperative radiotherapy for patients with stage pT3 and positive margins. In addition, adjuvant radiotherapy should be considered for stage pT3 with negative margins and pT2 with positive margins [1]. In the case of a recurring PSA elevation, salvage radiotherapy should be started early [2].

Three phase III trials demonstrated a superior biochemical recurrence-free survival (PSA-BFS) for adjuvant radiotherapy compared to surgery alone: EORTC 2291 [3], SWOG 8794 [4] and ARO 96–02 [5]. Additionally, an update of SWOG 8794 trial exhibited an advantage in overall survival for adjuvant radiotherapy [6]. While the toxicity profile of definitive radiotherapy is well characterised, data on side effects of adjuvant irradiation is relatively sparse. Patients in the EORTC trial showed more side effects in the radiotherapy arm, however, the rate of NCI CTC AE toxicities grade 3 or higher was comparable to the control arm. In the ARO trial, 3% of the irradiated patients suffered from acute, and 2% of late grade 3 bladder toxicities and 10% showed grade 2 late rectal toxicity.

Irradiation of the pelvic lymph nodes (whole pelvis radiotherapy, WPRT) in patients with a high risk of lymph node involvement according to the Roach formula is still subject to discussion. While some randomised trials could demonstrate a benefit for the WPRT in a definitive setting (RTOG 94–13 [7]), others could not (RTOG 77–06 [8], GETUG-01 [9]). For postoperative WPRT, Spiotto et al. [10] showed in a retrospective analysis of 160 high-risk patients an improved 5-year BFS.

In recent years, hypofractionated radiotherapy, i.e. the treatment with an increased daily dose, has gained importance in prostate cancer radiotherapy. The radiation-induced death of mammalian cells is a function of total dose, daily dose and treatment duration. The radiation sensitivity of normal tissues and cancer cells is described by the α/β value using the linear-quadratic model. The α/β value appears to be high (≥ 10 Gy) for so-called early-reacting tissues (e.g. skin, mucosa and most tumor cells) and low (< 5 Gy) for late-reacting tisuses (e.g. spinal cord and bone). Differences in the α/β values between normal tissues and tumor cells are the basis for developing fractionation regimes in radiation oncology. For prostate cancer cells, in vitro studies and retrospective analyses have indicated an α/β value as low as 1.5 Gy (and thus lower than the respective values for rectum and bladder), implying that patients with prostate cancer might benefit from treatment with high daily doses [11]. For primary radiotherapy, several non-randomised prospective trials have demonstrated comparable rates of acute and late toxicity and, in particular, similar efficacy when comparing hypofractionated and conventionally fractionated radiotherapy: Kupelian et al. [12] saw in a phase I/II trial when treating with 70 Gy in 2.5 Gy single doses a low rate of rectal toxicity and a biochemical disease control comparable to patients treated with conventional fractionation. An early analysis of an Italian phase III trial [13] comparing 62 Gy in 3.1 Gy single doses to 80 Gy in conventional fractionation reported a 3-year grade 2 rectal toxicity of 17% vs. 16% and grade 3 genitourinary (GU) toxicity of 14% vs. 11%. 3-year-BFS was significantly higher in the hypofractionated arm (87% vs. 79%, p=0,035). In line with these data, investigators of a randomised phase III trial [14] comparing 55 Gy in 2.75 Gy single doses with 64 Gy in 2 Gy single doses saw no difference in late gastrointestinal (GI) and GU toxicity, while the BFS rate at 90 months was statistically significantly higher in the hypofractionated group (53% vs. 34%).

While hypofractionated regimen are beginning to be integrated into clinical routine in first line treatment, data on postoperative hypofractionated radiotherapy is still sparse. Kruser et al. observed low toxicity rates in 108 patients treated with 65 Gy in 2.5 Gy single dose: Only one patients suffered from acute grade 3 GU toxicity and no acute grade 3 GI toxicities occurred. No patient suffered from any late grade 3 toxicity [15].

While the early trials on prostate radiotherapy have been conducted with conventional radiation techniques, it has been demonstrated that the dose to the prostate can be escalated with intensity-modulated radiotherapy (IMRT) without the risk of higher toxicity [16,17]. In addition, sophisticated imaging devices have been implemented in daily routine that can ensure exact dose application. Helical Tomotherapy (HT) constitutes a fusion of a linear accelerator with a spiral CT scanner, offering the possibility of MV-CT imaging with good soft tissue contrast before each treatment fraction combined with IMRT treatment with sharp dose gradients [18,19].

We initiated this phase II trial to investigate the toxicity profile and efficacy of a hypofractionated postoperative radiotherapy of the prostate bed with or without the inclusion of the pelvic lymph nodes using HT under daily image guidance.

## Methods/design

### Study design

The PRIAMOS trial is a single-center, non-randomised prospective two-arm prospective phase II trial. Patients will be stratified according to their risk of lymphatic involvement into either hypofractionated radiotherapy of the prostate bed alone with 54 Gy in 18 fractions of 3.0 Gy each (low risk of lymph node involvement, arm 1, PRIAMOS 1) or additional simultaneous treatment of the pelvic lymph nodes with 45 Gy in 18 fractions of 2.5 Gy (high risk of lymph node involvement, arm 2, PRIAMOS 2). Patients eligible for the PRIAMOS trial have to present with the indication for a radiotherapy of the prostate bed. Patients with a risk of lymph node involvement of >20% according to the Roach formula [20] (2/3 PSA + [Gleason - 6] x 10) with inadequate lymphadenectomy (< 10 lymph nodes) and patients with positive resected nodes (pN1) are attributed to arm 2 and receive a simultaneous treatment of the pelvic lymph nodes. For the trial flowchart, see Figure 1.

**Figure 1 F1:**
[figure not shown]
Trial flowchart.

### Study objectives

The main objective is to demonstrate the safety and feasibilty of a hypofractionated helical IMRT of the prostate bed with (PRIAMOS 2) or without (PRIAMOS 1) the pelvic lymph nodes. Treatment safety will be judged by the incidence of NCI CTC AE grade 3–4 toxicity and by occurrence of treatment discontinuation.

Secondary objectives are BFS, quality of life (QoL) and clinical symptoms. A biochemical recurrence is defined as 3 consecutive rises in PSA levels (ASTRO criteria). QoL is investigated using the EORTC QLQ-C30 and QLQ-PR25 questionnaires; symptoms and toxicities will be graded using the NCI CTC AE version 4.0 grading criteria.

### Trial organisation

The PRIAMOS trial is a single-center, investigator-initiated trial carried out by the Department of Radiation Oncology, University Hospital of Heidelberg, Germany.

### Patient selection: inclusion criteria

Patients meeting all of the following criteria are eligible for the PRIAMOS trial:

resected prostate carcinoma with histological grading (Gleason Score)

status post prostatectomy for a pT3 carcinoma and/or R1/2 resection or PSA recurrence after prostatectomy (2 consecutive PSA rises)

PSA recurrence ≥ 1 ng/ml: CT/PET/MRI imaging excluding pathological lymph nodes

Karnofksy performance score ≥ 70%

age 18–80 years

only arm 2: antihormonal therapy for 2 months prior to radiotherapy and continuation of hormonal suppression after radiotherapy recommended

written informed consent

### Patient selection: exclusion criteria

Patients meeting at least one of the following criteria are not eligible for the PRIAMOS trial:

patient‘s refusal

patient‘s inabillity to give informed consent

stage IV (distant metastases)

lymph node involvement outside the pelvis

severe wound complications after laparatomy

only arm 2: severe lymphoedema of the legs, elephantiasis, postthrombotic syndrome

decompensated pulmonary, cardiovascular, metabolic, hematopoetic, coagulatory or renal comorbidities

known other malignant disease with distant metastases

prior pelvic irradiation

participation in another clinical trial that might compromise the results of the PRIAMOS trial or the other trial

### Statistical design

Each of the two arms (PRIAMOS 1 and PRIAMOS 2) is designed an independent single stage phase II trial with the safety and feasibility the respective treatment as primary endpoint, precisely defined as the proportion SDR of patients with no NCI CTC AE grade 3–4 toxicity and no discontinuation of treatment during the full set of 18 fractions by any reasons in the intent-to-treat (ITT) population. The ITT population is defined by compliance with the in- and exclusion criteria and not dropping out within one week after start of treatment.

The study hypothesis is chosen as H1: SDR≥ 95% to be tested versus the null hypothesis of H0: SDR≤ 80% using a single arm exact binomial test for proportions. In order to test H0 versus H1 one-sided at the significance level of 0.10 (10%) n= 32 evaluable patients are required to achieve a power of 90%, when using PASS software and A’Hern [21] and choosing the type I and the type II error identical for such a phase II trial. In order to compensate possible drop out between informed consent and treatment for at least one week n=40 patients are planned to be recruited per arm.

No formal interim analysis is scheduled. However, recruitment is put on hold in an arm when the proportion SDR surpasses the critical number of 4. The study coordination team will then decide on stop of recruitment of the respective as well as the other trial arm.

Statistical evaluation of the primary endpoint as well as of the secondary endpoints BFS, QoL, overall survival and detailed safety analysis will be performed separately for each arm, for the ITT (SDR, BFS, QoL) as well as for the per protocol (PP; SDR,BFS) and the safety (SF; QoL, NCI CTC AE) population. Statistical comparisons between the two trial arms are performed exclusively with descriptive intention.

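### The primary analysis set, labelled ITT, leaves out patients who drop out in the first week of treatment, although the endpoint counts them as failures

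*Protocol article*

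**What the plan says.** All of the following is in the protocol article.

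- **Endpoint (Statistical design).** SDR is the proportion of patients with no grade 3–4 toxicity and "no discontinuation of treatment during the full set of 18 fractions by any reasons".
- **Population (Statistical design, next sentence).** "The ITT population is defined by compliance with the in- and exclusion criteria and not dropping out within one week after start of treatment".
- **Test (Statistical design).** SDR of at most 80% is tested against SDR of at least 95%, one-sided at 0.10, "using a single arm exact binomial test for proportions". The plan requires 32 evaluable patients per arm for 90% power.
- **Recruitment (Statistical design).** 40 per arm are planned. The extra patients cover losses from consent up to one week of treatment, so patients who start and leave within the week are treated as replaceable.
- **Other populations (Statistical design).** SDR is analysed in the ITT and per-protocol sets. The safety set covers quality of life and graded toxicity, not SDR.
- **Schedule (Radiation therapy).** The 18 fractions are given daily, Monday to Friday.
- **Objective (Study objectives).** Safety is judged by grade 3–4 toxicity and by treatment discontinuation.

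**The concern.** The two consecutive sentences in Statistical design cannot both govern the primary analysis. A patient who stops at fraction 3 has failed under the first and is absent under the second. Membership of the analysed set depends on something that happens after treatment starts and that is itself part of the endpoint.

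Only the denominator changes, because a patient who discontinues was never among the successes. With s successes among N starters, of whom k leave in week 1, the plan reports s/(N − k) instead of s/N, which is never smaller. The error therefore runs in one direction, towards declaring the regimen safe and feasible. The rule allows only 3 failures in 32, so each removed failure counts. The ITT label would also lead a reader to believe that early stoppers had been included.

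**Working it through.** **Inputs from the article:** null SDR 0.80, alternative 0.95, one-sided alpha 0.10, power 0.90, 32 evaluable and 40 recruited per arm. **Assumption:** a share w of starters leaves in week 1, each of them a failure under the endpoint. The article gives no value for w; 0% to 10% is shown.

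**1. The plan's own figure.** I looked for the smallest n with a cut-off r such that P(X ≥ r | n, 0.80) ≤ 0.10 and P(X ≥ r | n, 0.95) ≥ 0.90. The result is n = 32 with r = 29, that is, at most 3 failures. Exact alpha is 0.0931 and power 0.926. No n from 20 to 31 meets both limits. So n = 32 is reproduced, and 32/0.80 = 40.

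**2. Effect of the exclusion under the null.** If SDR among all starters is 0.80 and the share w is removed, SDR among those left is 0.80/(1 − w). For example, 0.80/0.95 = 0.842. The type I error for starters is then P(X ≥ 29 | 32, 0.80/(1 − w)). The last column instead lets 40 patients start, draws the number of week-1 dropouts from Binomial(40, w), and applies the exact 0.10 test to those left.

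| w | SDR among those left | Type I error, 32 evaluable | Type I error, 40 starters |
|---|---|---|---|
| 0% | 0.800 | 0.093 | 0.076 |
| 1% | 0.808 | 0.113 | 0.099 |
| 2% | 0.816 | 0.136 | 0.126 |
| 5% | 0.842 | 0.234 | 0.216 |
| 10% | 0.889 | 0.518 | 0.465 |

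The nominal 0.10 is exceeded at 1% with 32 evaluable patients. With 40 starters it is just met at 1% and exceeded at 2%.

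**3. One patient.** Suppose 33 start, 1 stops in week 1 and 3 fail later.
- As written: 29/32 = 90.6%, P(X ≥ 29 | 32, 0.80) = 0.093, null rejected.
- All starters: 29/33 = 87.9%, P(X ≥ 29 | 33, 0.80) = 0.18, null not rejected. With 33 patients, 30 successes are needed.

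**4. What the correction does to power.** If all 40 start and are analysed, the rule is at least 36 successes, with alpha 0.076 and power 0.952 at SDR 0.95. If the 95% was meant only for patients who remain after week 1, SDR among starters is 0.95(1 − w):
- w = 2.5%: 0.95 × 0.975 = 0.926, power 0.83.
- w = 5%: 0.95 × 0.95 = 0.9025, power 0.65.

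**The case against.** **The inflation depends on an unstated rate.** This stands. If nobody leaves in week 1 there is none. At w = 10%, half of the 20% failures allowed under the null would have to fall in about the first 5 of 18 fractions. The postoperative series described in the Background had one acute grade 3 genitourinary event in 108 patients and no acute grade 3 gastrointestinal toxicity. It gives no discontinuation rate, but nothing in it points to early losses of that order. A reader might infer from the upper rows of the table that the trial's real type I error is 0.2 or 0.5; the article does not support any particular value.

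**For the population as defined, the test is valid.** This is true but beside the point. The exact alpha of 0.093 holds for patients who remain after a week, while the endpoint wording and the main objective concern discontinuation over the whole course.

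**Dropping out may mean leaving the study, not stopping radiotherapy.** The two sentences do use different words, so some ambiguity remains. The sample-size sentence, which speaks of loss before a week of treatment has been given, favours the reading taken here. If the narrower meaning was intended, the text should say so.

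**Early toxicity is still reported.** The safety set may well show it, so it would be wrong to infer that such events vanish from the trial report. That does not return these patients to the SDR test.

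**A wider reading that does not hold.** The analysis set also requires compliance with the inclusion criteria, and one of these reads "only arm 2: antihormonal therapy for 2 months prior to radiotherapy and continuation of hormonal suppression after radiotherapy recommended". A reader might infer that arm-2 patients could be removed for what they do after radiotherapy. The line only recommends, and eligibility is judged at entry, so the document does not support this.

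**Conclusion.** The contradiction is in the stated text and does not depend on anything left to a fuller document. Week-1 stoppers are failures by the endpoint definition and are removed by the population definition, and nothing in the article returns them to the SDR analysis. The bias relative to all starters can only be upward. Its size is conditional: none without week-1 dropout, modest at 1–2% (type I error 0.113–0.136 with 32 evaluable patients), and large at 5% or more (0.234 and above). These figures assume a true SDR of exactly 80% among starters and that every week-1 dropout is a stop of treatment. The sample size of 32 is correct for the stated hypotheses. Leaving out patients who never start is defensible for a treatment-safety endpoint. The point should be corrected because it affects the primary result and one patient can change the conclusion.

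**What to change.** Define the primary analysis set as all eligible patients who receive at least one fraction. Count any discontinuation before completion of the 18 fractions, week 1 included, as an SDR failure. Keep the one-week set as a labelled sensitivity analysis, and reserve the term ITT for a set that does not depend on staying on treatment. Patients who consent but never start may still be excluded and are covered by the planned 40 per arm. State the cut-off for the number actually analysed, for example at least 29 of 32 or at least 36 of 40.

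With early stoppers counted, the 29-of-32 rule keeps its exact alpha of 0.093 at an SDR of 80% among starters, whatever the week-1 dropout.

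**Cost.** The change is in wording and needs no increase in planned recruitment if the 95% alternative refers to all starters. The SDR estimate may be less favourable. If the 95% refers only to patients who remain after week 1, power with 40 starters falls from 0.95 to 0.83 at 2.5% week-1 dropout and 0.65 at 5%. The plan should therefore say which group the 95% describes, and recheck the sample size if it is the narrower one.

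### The recruitment-hold rule compares a success proportion with a count of 4; read as failures, exceeding 4 fits 38 to 40 evaluable patients, not the stated 32

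*Protocol article*

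**What the plan says.** All of this stands in the protocol article under Statistical design.

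- **Endpoint.** The primary endpoint in each arm is "the proportion SDR of patients with no NCI CTC AE grade 3–4 toxicity and no discontinuation of treatment during the full set of 18 fractions". SDR is therefore a success proportion between 0 and 1, and higher is better.
- **Hypotheses.** The text sets "The study hypothesis is chosen as H1: SDR≥ 95" percent against the "null hypothesis of H0: SDR≤ 80" percent.
- **Test.** It is carried out "using a single arm exact binomial test for proportions", "one-sided at the significance level of 0.10 (10" percent).
- **Size.** "n= 32 evaluable patients are required to achieve a power of 90" percent, and "n=40 patients are planned to be recruited per arm" to cover drop-out.
- **Hold.** No formal interim analysis is planned, but "recruitment is put on hold in an arm when the proportion SDR surpasses the critical number of 4". The coordination team then decides whether recruitment stops in that arm and in the other.

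The article does not print the rejection boundary of the test. It does not say that the 4 counts failures, or which number of patients the 4 belongs to.

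**The concern.** The hold sentence conflicts with the endpoint definition in the same section, in both unit and direction. A proportion is compared with a whole number above 1, and a high value of a success measure is made the alarm. Someone applying the sentence as printed would never hold an arm. Someone who took SDR as a number of patients would hold it on good results.

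The natural repair is to read the 4 as a number of patients failing SDR. That raises a second question: does exceeding 4 failures agree with the exact test on which the arm was sized?

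The stakes are practical. This is the only arm-level hold that the article describes; Monitoring during treatment covers individual patients only. The primary endpoint is safety and feasibility, and the Discussion says that the authors know of no clinical data on hypofractionated treatment of the pelvic nodes. A hold in one arm also opens a decision on the other arm. The trigger should be usable without guesswork.

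**Working it through.** **Inputs** (Statistical design): p0 = 0.80, p1 = 0.95, one-sided alpha 0.10, power 90%, exact binomial test, 32 evaluable and 40 recruited per arm.

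Let F be the number of patients failing SDR among n evaluable patients. H0 is rejected when F ≤ c, where c is the largest integer with

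P(F ≤ c | n, 0.20) = Σ (k = 0 to c) C(n,k) · 0.20^k · 0.80^(n−k) ≤ 0.10.

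Power is P(F ≤ c | n, 0.05).

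**Step 1: reproduce the plan's figure.** The smallest n that meets both error limits is 32, with c = 3 (at least 29 successes), alpha 0.0931 and power 0.9262. At n = 31 the boundary is c = 2 and power is only 0.799. The stated 32 is confirmed.

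**Step 2: the sentence as printed.** SDR ≤ 1 < 4 always, so the condition is never met. As a count of patients with SDR, more than 4 means the fifth success.

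**Step 3: the sentence read as failures.** More than 4 means F ≥ 5. The boundaries from the stated test are:

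| Evaluable n | Most failures that still reject H0 | Exact alpha | Power at SDR 95% |
|---|---|---|---|
| 32 | 3 | 0.093 | 0.926 |
| 33 | 3 | 0.081 | 0.919 |
| 34 | 3 | 0.070 | 0.912 |
| 35 | 3 | 0.061 | 0.904 |
| 36 | 3 | 0.052 | 0.896 |
| 37 | 3 | 0.045 | 0.888 |
| 38 | 4 | 0.099 | 0.960 |
| 39 | 4 | 0.087 | 0.956 |
| 40 | 4 | 0.076 | 0.952 |

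At n = 32, F ≤ 4 has probability 0.204 under H0, so 4 failures cannot reject. At n = 40, F ≤ 5 has probability 0.161, so 5 failures cannot reject there either. If the arm ends with 32 to 37 evaluable patients, the fourth failure rules out rejection. If it ends with 38 to 40, the fifth does.

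**Step 4: chance of a hold.**

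| Patients observed | True SDR | Hold at 4th failure, P(F ≥ 4) | Hold at 5th failure, P(F ≥ 5) |
|---|---|---|---|
| 32 | 80% | 1 − 0.0931 = 0.907 | 1 − 0.2044 = 0.796 |
| 32 | 95% | 1 − 0.9262 = 0.074 | 1 − 0.9796 = 0.020 |
| 40 | 80% | 0.972 | 0.924 |
| 40 | 95% | 0.138 | 0.048 |

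The mismatch is one failure. Over 32 patients it changes the chance of holding an arm with SDR 80% by 0.907 − 0.796 = 0.111.

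**The case against.** The best defence is that the intended meaning is easy to guess and that 4 is a sensible number once failures are understood. While an arm is recruiting, its final evaluable number is unknown and may reach 40. More than 4 failures is the first point at which H0 cannot be rejected for any evaluable number from 32 to 40, which is a coherent reason to hold. This stands: the number fits the recruited 40, though not the 32 that the design rests on. The article does not say which was meant.

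Two stronger readings are tempting, and the document does not support them.

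- **A reader might infer that an arm with 4 failures among 32 patients has already lost its test.** That is so only if evaluable accrual ends at 37 or fewer. With no further failure, 4 of 38 (alpha 0.099) or 4 of 40 (alpha 0.076) still rejects H0. At a true SDR of 95%, six further successes have probability 0.95^6 = 0.74 and eight have 0.95^8 = 0.66.
- **A reader might infer that the type I error rises to about 20%.** The 0.204 would apply only if 4 failures in 32 counted as success. Nothing says so: the final analysis is the exact test at one-sided 0.10, and the hold leads to a decision by the coordination team, not to a test result.

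The article also condenses a protocol that is not shown. The full text may word the rule correctly or contain other safeguards, so the point concerns the printed sentence and not the whole trial's safety oversight. None of this makes that sentence usable as it stands.

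**Conclusion.** The point holds as a wrongly stated decision rule. As printed, the hold either cannot trigger or triggers on successes. On the charitable reading it is one failure later than the boundary for the stated 32 evaluable patients, and consistent with 38 to 40. The sample size is right, and the alpha of the final test is untouched.

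The numerical part assumes that the 4 was meant to count patients failing SDR, that the hold was meant to follow the boundary of the primary test, and that patients are independent with a common SDR. The contradiction between a proportion and a count needs none of these assumptions.

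**What to change.** Restate the rule as a count of patients failing SDR, with failure as the protocol defines it: grade 3–4 toxicity or discontinuation. Say whether the hold comes on reaching or on exceeding the number. Tie the number to a planned final evaluable n fixed in advance, because the actual n is not known during accrual:

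- **Reference 32:** hold when failures exceed 3.
- **Reference 40:** hold when failures exceed 4.

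The sponsor should choose the reference and state it. Separately, give the final rejection boundary by actual evaluable n: at most 3 failures for 32 to 37, at most 4 for 38 to 40.

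The cost is one sentence and a two-row table. With the 32 reference, the hold comes one failure earlier than at the fifth. A failing arm is caught sooner, but a good arm is held more often (at SDR 95%, 0.074 instead of 0.020 within 32 patients). Some held arms could still have rejected H0 had 38 to 40 patients become evaluable. With the 40 reference, an arm that ends with 32 to 37 evaluable patients may reach a fourth failure, and so be unable to reject H0, without having been held.
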